### Study Outcomes and Statistical Analysis

#### Primary Hypothesis

The primary hypothesis is that display of predictive analytics monitoring on acute care cardiology wards increases the number of hours free from clinical deterioration.

The primary outcome is the number of hours free from clinical deterioration (acute clinical events) within 21 days of admission. Hours of acute clinical events are defined as the time when one or more of the variables found in Textbox 1 occur. A maximum score will be 21 event-free days (504 hours). Patients who are discharged from the hospital prior to 21 days without an event will be counted as having 21 event-free days (504 hours). Patients who die during the admission will be counted as having 0 event-free days (0 hours). As an example, a patient who has an emergent ICU transfer on hour 26 of their admission will have 25 event-free hours. Patients will be censored (with no event observed) at the time of nonemergent ICU transfer (ie, for planned bronchoscopy), nonemergent surgery transfer, or other transfer (change in bed assignment) because a change in bed assignment can result in a change in randomization allocation (as carry over could occur in patients who have a display and then become “undisplayed”). We will conduct a randomized (formerly called “intent-to-treat”) analysis, in which all available data on all randomized participants are included for the primary end point comparison between intervention and usual care.

For the primary outcome (hours free of an acute clinical event), the primary analysis will employ a generalized estimating equation (GEE) with Poisson link. This model will be able to handle the multiple levels of correlation in the study design—patients within a cluster and potentially different intervention arms within a patient who has an event and then returns to the ward—as well as differences in the amount of time at risk for each patient that is censored.

Study outcomes by hypotheses.

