**Hypotheses 2 and 4**
1. Proportions of the following individual events at any point in the hospital stay after admission to the fourth floor:Emergent ICU transfer (emergent defined as urgent, unplanned)Emergent intubation (emergent is defined by clinician’s notes as a nonplanned procedure)3 units or more of blood ordered in 24 hoursinotropes or vasopressor useShock requiring inotropes or vasopressorsSepsis (sepsis-2 definition)Septic shock requiring inotropes or pressors (defined by a combination of the 2 above criteria)Cardiac arrestDeathDiuretic drip indicating congestive heart failure escalationInotropes or pressors for heart failureEmergent surgery prior to ICU transfer (emergent is defined by clinician’s notes as a nonplanned procedure)2. Hospital length of stay3. In patients who are never transferred to the ICU, the length of stay on the acute care floor4. ICU length of stay5. Proportion with readmission to hospital within 72 hours postdischarge6. In patients who meet the sepsis-2 criteria, the proportion of shock (ie, hypotension requiring inotropes or pressors), and death7. Number of days on intravenous antibiotics8. Number of days on intravenous anti-infectives9. Total duration of mechanical intubation (emergent and nonemergent)10. Impact of sex on outcome

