#### Sample Size, Power Analysis, and Attrition

We expect 11% of participants to drop out of the primary outcome because they will be in a room that switches the randomization arm at the time when rooms are rerandomized or because they will transfer rooms during their admission to a room of the opposite randomization or to a nonstudy room. We have accounted for this attrition in clinical trial planning and sample size considerations. The number of admissions to a room which will undergo cluster randomization is estimated to be 10,424. The study type 1 error rate will be set to 5% and the type II error rate to 20% (80% power). Additionally, an interim analysis will prespecified after half of the participants have completed their primary outcomes assessment. The interim analysis will use an O’Brien-Fleming spending function, giving nominal α values of .003 (interim) and .047 (final) for the 2 analyses. Should the primary outcome cross a stopping boundary at the interim analysis, the data safety monitoring board (DSMB) will have the option of stopping the study early.

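### The primary model keeps post-event returns to the ward under a possibly different arm, although the article elsewhere ends follow-up at arm changes because of carry-over

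*Protocol article*

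**What the plan says.** All references are to the protocol article.

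- **Primary Hypothesis, censoring.** "Patients will be censored (with no event observed) at the time of nonemergent ICU transfer", and likewise at a nonemergent surgery transfer or any other change of bed. The reason given is that "a change in bed assignment can result in a change in randomization allocation (as carry over could occur in patients" who lose the display.
- **Primary Hypothesis, model.** The next paragraph names a Poisson GEE and says that it can handle several levels of correlation, among them "potentially different intervention arms within a patient who has an event and then returns to the ward".
- **Primary Hypothesis, scoring.** The outcome is one number of hours out of 504 within 21 days of admission. In the worked example, "a patient who has an emergent ICU transfer on hour 26 of their admission will have 25 event-free hours". A patient who dies during the admission scores 0 hours.
- **Sample Size, Power Analysis, and Attrition.** An expected 11% drop out of the primary outcome because their room switches arm at rerandomization, or because they move to a room of the other arm or a nonstudy room. "The number of admissions to a room which will undergo cluster randomization is estimated to be 10,424".
- **Textbox 1, Hypotheses 2 and 4.** Individual events are counted "at any point in the hospital stay after admission to the fourth floor".

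**The concern.** Carry-over runs forward in time. A patient who had the display and then lost it is affected in the later stay, not the earlier one. The censoring rule follows that logic and stops the clock at the move. The model paragraph does the opposite for patients who have had an event: the later stay enters the primary analysis under the new room's arm, with the GEE offered as the remedy.

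That remedy addresses a different problem. The working correlation and robust variance of a GEE deal with dependence between records from one patient or cluster. They do not correct a mean that earlier exposure has shifted. Nor do they address selection: a re-entry record exists only if the patient survived a first event, which happens after randomization and which the first arm may influence.

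The affected patients have already deteriorated, so their later records may carry more than their share of events. What is at stake is some loss of contrast in the primary comparison, and a primary data set whose contents depend on which paragraph the programmer follows.

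**Working it through.** **Setting the rules side by side**

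| Situation | Rule in the article |
|---|---|
| Bed change without an event | Censored, because the arm may change and carry-over could occur |
| Move to an opposite-arm room | Dropout from the primary outcome, within the 11% |
| Event, then return to the ward, possibly in the other arm | Handled within the primary GEE |
| Event at hour 26 | One score for the admission, 25 hours |
| Death during the admission | One score for the admission, 0 hours; no arm named if the patient was in both |

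The third row conflicts with the first two in its reasoning. It also fits poorly with the last two: if scoring stops at the first event, a re-entry record has nothing to add; if it does not, one admission yields more than one score.

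**The plan's own figure.** The 10,424 is an expected number of room admissions. The article gives no effect size, standard deviation, event rate or intracluster correlation, so it cannot be rebuilt here, and that is not called an error. After the stated attrition, 10,424 × 0.89 = 9,277.

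**Size of the loss in the primary contrast.** The inputs are assumptions, except where noted:

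- s, the share of records that are re-entries: 2.5% to 10%.
- m, the event rate in re-entry records relative to first entries: 1 to 5.
- k, the share of the display effect that persists into usual-care time: 50% to 100%.
- Half of returns go to the opposite arm. The Randomization Process section says that room placement is not influenced by arm, which supports this but does not prove it.
- Nominal power 80% (the article's target) and a two-sided 5% test (sidedness of the primary test is not stated).

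Formulas:

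- Share of events from re-entries: w = s·m / (1 − s + s·m)
- Share of the effect kept = 1 − 0.5·w·k
- Power = Φ(kept × (1.960 + 0.842) − 1.960)

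For s = 0.05, m = 5, k = 1: w = 0.25 / (0.95 + 0.25) = 0.208; kept = 1 − 0.5 × 0.208 = 0.896; power = Φ(0.896 × 2.802 − 1.960) = Φ(0.55) = 0.709.

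| s | m | k | w | Effect kept | Power |
|---|---|---|---|---|---|
| 0.025 | 1 | 0.5 | 0.025 | 0.994 | 0.795 |
| 0.05 | 1 | 1 | 0.050 | 0.975 | 0.780 |
| 0.05 | 3 | 1 | 0.136 | 0.932 | 0.742 |
| 0.05 | 5 | 1 | 0.208 | 0.896 | 0.709 |
| 0.10 | 5 | 1 | 0.357 | 0.821 | 0.634 |

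With re-entries at 5% of records or fewer, about 1% to 10% of the effect is lost. The last row, with twice that share, loses 18%.

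**A check in counts.** Assume that 5% of 10,424 stays have an event, 80% of those patients return, and 15% of returners have a second event. The only 5% in the article, in the Introduction, is a frequency of subacute illness and not of the trial composite, so this is an illustration.

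- First events: 0.05 × 10,424 = 521
- Re-entries: 0.8 × 521 = 417, equal to 4.0% of 10,424; about 208 of them (2.0%) in the opposite arm
- Second events: 0.15 × 417 = 63, so w = 63 / (521 + 63) = 0.107
- With full carry-over, kept = 1 − 0.5 × 0.107 = 0.946. A true 20% reduction appears as about 19%, and power falls from 80% to about 76%.

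**The case against.** The strongest reply is that the contaminated time may never enter. The hour-26 example reads as scoring to the first event, and the attrition text treats opposite-arm moves as dropout; on that reading a return adds nothing. But then the model sentence is wrong. Other wording points the other way: event hours are defined as a duration, Textbox 1 lists the ICU stay together with the emergent transfer (which leaves room for event-free hours afterwards), and the analysis is to include all available data on everyone randomized. The text needs correcting under either reading.

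A second reply is that returning patients are placed without regard to arm, so analysing each room admission by its own arm is a legitimate estimand. It can be defended, but not together with a rule that ends follow-up at other bed changes because of carry-over.

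A third is that an article leaves such detail to the full protocol or analysis plan. That would answer a missing rule. Here the article states the rule and offers a remedy that does not suit the problem.

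A reader might also infer that whole-stay events and costs are counted in both arms for a patient who was in both. The article does not say so. Textbox 1 gives a time window, the Secondary Hypothesis section names a GEE, and the cost analysis compares the two groups; none assigns a two-arm stay to both. The full documents may settle the arm, so this is not part of the point.

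**Conclusion.** The point holds as an internal conflict in the primary analysis. Carry-over ends follow-up for moves without an event, while returns after an event stay in the model under a possibly different arm, and the GEE does not repair the carry-over or the selection on surviving a first event.

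The likely loss is small to moderate: roughly 1% to 10% of the effect if re-entries are at most 5% of records, with nominal 80% power becoming about 71% to 79.5%. This rests on assumed re-entry shares, event rates and carry-over, and on an even split of returns between arms. The calculation takes the 80% as given and does not model clustering.

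A reader might conclude that the results are necessarily pulled toward no effect. That is the usual direction if the display effect persists, but it is not certain. If returns favour the original room or arm, high-risk re-entry records would fall unevenly between the arms, and the bias could run the other way.

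**What to change.** - **Primary analysis:** use one record per hospitalization, the first stay in a randomized bed, analysed in that bed's arm. Follow-up ends at the first event or at the censoring already stated. Name the arm of the first randomized bed as the one that takes the 0 hours for a death.
- **Sensitivity analysis:** add post-event re-entries, with prior display exposure as a covariate.
- **Text:** remove or reword the model sentence on different arms within a patient, and reconcile the Primary Hypothesis and sample-size sections on moves to an opposite-arm room.
- **Companion rule, for consistency:** count each whole-stay Hypothesis 2 and 4 outcome, and the costs, once, in the arm of the first randomized bed.

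The cost is mainly wording, since the planned data extraction already covers what is needed. The primary analysis loses a few percent of records (about 4% in the illustration), the 10,424 room admissions must be restated as hospitalizations, and whole-stay outcomes keep some dilution in patients who later change arm.

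### The Poisson GEE on event-free hours handles censored time at risk only under an exposure definition that the protocol does not give

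*Protocol article*

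**What the plan says.** In the Protocol article, Primary Hypothesis, the response is a duration: "The primary outcome is the number of hours free from clinical deterioration (acute clinical events) within 21 days of admission". The scoring rules are:

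- Discharge without an event: "Patients who are discharged from the hospital prior to 21 days without an event will be counted as having 21 event-free days (504 hours".
- Event: the hours before it. In the article's example, "a patient who has an emergent ICU transfer on hour 26 of their admission will have 25 event-free hours".
- Death at any time in the admission: 0 hours.
- Censoring: "Patients will be censored (with no event observed) at the time of nonemergent ICU transfer". The same applies to nonemergent surgery transfer and to any other change of bed. No score or exposure is given for these patients.

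The primary model is a GEE described as having a Poisson link. Among the features it is said to handle is "differences in the amount of time at risk for each patient that is censored". No offset or weight is named. The section also keeps every randomized participant in the comparison with whatever data they have.

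Sample Size, Power Analysis, and Attrition describes patients whose room switches arm, or who move to the opposite arm or off the study rooms, differently: "We expect 11% of participants to drop out of the primary outcome".

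**The concern.** A Poisson model copes with unequal follow-up when the response counts events and the offset is the log of time at risk. Here the response is time. The model has no risk set and no censoring mechanism; an offset only rescales each patient's expected hours. Discharged patients are also credited with hours in which nobody observed them. The assurance therefore does not follow from the method named. Two ordinary ways of programming it would make the primary test measure bed moves or length of stay instead of deterioration.

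The scoring rules also collide. A patient censored at a bed change who later dies in the same admission is censored with no event under one rule and scored 0 under another. A patient who changes room is censored and kept under one section, and lost to the primary outcome under another.

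**Working it through.** **The plan's own figures.** 21 × 24 = 504 h, and an event on hour 26 leaves 26 − 1 = 25 h. Both reproduce. The 10,424 admissions and 80% power cannot be re-derived, because the article gives no effect size, SD or intracluster correlation. The powers below therefore only compare one specification with another.

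**How much of the 504 h is credited.** Take 85 beds, 20 months (20 × 30.4375 = 608.75 days) and 10,424 admissions. At full occupancy the mean ward stay is at most 85 × 608.75 / 10,424 = 4.96 days, or 119 h. For a discharge at that stay, 1 − 119/504 = 76% of the score was not observed.

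**Score per patient.** A censored patient's response is taken as the hours observed, since the article gives none.

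| Patient | No offset | Offset: hours at risk | Offset: 504 h, or censoring time if censored |
|---|---|---|---|
| Emergent ICU transfer on hour 26 | 25 | 25/26 = 0.96 | 25/504 = 0.05 |
| Censored after 25 h | 25 | 25/25 = 1.00 | 25/25 = 1.00 |
| Event-free discharge at 96 h | 504 | 504/96 = 5.25 | 504/504 = 1.00 |
| Event-free discharge at 60 h | 504 | 504/60 = 8.40 | 504/504 = 1.00 |
| Death | 0 | 0 | 0 |

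The first column cannot tell a bed move from a deterioration. In the second, the event and the censored patient are nearly equal, and the large differences come from how soon patients go home. The third separates events from the rest.

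**Effect on the test.** With arm as the only covariate, a log link and independence working correlation, the estimate is the ratio between arms of (sum of scores)/(sum of exposures). It was simulated for 10,424 admissions split equally.

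The 11% is the article's attrition figure, used as a proxy for the share censored. The 5% is its figure for subacute illness, not for this composite. Also assumed: 20% of events fatal, censoring spread uniformly over the stay, no clustering.

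Power at a hazard ratio of 0.80 and a mean stay of about 119 h, with the range over repeated runs:

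- complete data: 65%
- no offset: 20-24%
- hours at risk: 3-4%
- 504 h or censoring time: 62-63%

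A second set used 5% v 3.75% events, mean stay 3 or 4.5 days and a two-sided test at .047. Power was 33-35%, 5% and 83-84% in the same order of offsets. With 30% censored in both arms it was 14%, 4% and 83%.

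The loss without an offset has a simple source. At a mean stay of 4.5 days, the mean shortfall from 504 h is 70.0 h, of which 48.4 h (48.4/70.0 = 69%) comes from censored patients and 21.6 h from events.

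**No true difference in events (second set).**

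- Censoring and stay equal: rejection in about 3-6% of runs under all three specifications.
- No offset, 13% v 11% censored: ratio 0.980, false harm in 71-74%. At 9% v 11%: ratio 1.020, false benefit in 76%.
- Hours at risk, stay 5% shorter: ratio 1.052, false benefit in 92-93%. Stay 5% longer: ratio 0.953, false harm in 89-92%.
- 504 h or censoring time, in the same scenarios: ratio 0.9994 to 1.0006.

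**The case against.** The article names no offset, and a journal article may leave that to the analysis plan, so its absence alone is no finding. The quoted words speak of adjusting for censored patients. A model with no offset would do nothing of the kind, and event-free discharges are not censored, so nothing in the text says to divide their 504 h by the observed stay. An exposure of 504 h unless censored fits the wording and avoids both faults. Leaving censored patients out, as the attrition paragraph suggests, also largely avoids them: with 13% v 11% censored and no effect, the mean then shifts by about −0.3 h, against about −8.5 h with no offset.

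Most of this stands. A reader might infer that the plan is bound to one of the two failing specifications; the documents do not support that. A reader might also infer a high false-positive risk. Those rates need censoring or stay to differ by arm. The article gives no such difference, and it says that bed placement is not influenced by allocation. An unblinded display meant to change care could shift transfers or stay, but the size of any shift is an assumption.

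What remains is that the article asserts that the model handles censoring. Time at risk, in its ordinary sense, gives the failing offset: a patient discharged on day 4 is not at risk for 504 h. Leaving patients out conflicts with keeping everyone randomized in the comparison.

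**Conclusion.** The stated method does what is claimed only under an exposure definition that is absent from the text and is not time at risk in the usual sense. Under the assumed inputs, the choice moves power from about 62% to about 20-24% (no offset) or 3-4% (hours at risk). With censoring and stay equal between arms, that loss of power is the cost; false-positive results arise only if one of them differs by arm. The power figures rest on assumed event rate, fatality, stay and effect, and ignore clustering; the per-patient scores rest only on the article's rules and on counting a censored patient's observed hours.

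The 11% may understate censoring. It covers arm switches and moves to the opposite arm or a nonstudy room, whereas the censoring rule also takes in any other bed change and nonemergent ICU or surgery transfers.

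The two conflicts in the scoring rules hold whatever offset is intended.

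**What to change.** 1. Preferably, analyse restricted mean event-free hours to 504 h, for example with Kaplan-Meier pseudo-observations in a GEE with identity link, clustered as planned. Carry event-free discharges to 504 h, score deaths by the stated rule and treat bed changes as censored.
2. If the Poisson GEE is kept, specify a log link with offset log(504) for every uncensored patient and log(censoring time) for censored patients. State that this assumes censoring unrelated to risk. It is not exact: with no true difference and 20% v 11% or 30% v 20% censored, the ratio was 0.997-0.998 and false harm appeared in 7-9% of runs (12% at a 10% event rate), against a nominal 0.047/2 = 2.35% per side.
3. State which score applies when a patient censored at a bed change later dies in the same admission.
4. Reconcile the attrition paragraph with the Primary Hypothesis section: say whether room-changers are censored and kept, or left out.

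The cost is wording and a little programming, with no new data or patients. It should be settled before the interim analysis, which tests the same outcome. A sensitivity analysis counting nonemergent transfers as events is optional and not part of this point.

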**Hypothesis 1 (primary study outcome)**
1. Hours free from the following:An emergent intensive care unit (ICU) transfer (emergent defined as urgent, unplanned) and ICU stayEmergent intubation (emergent is defined by clinician’s notes as a nonplanned procedure)Cardiac arrest, if prior to ICU transferDeathEmergent surgery prior to an ICU transfer (emergent is defined by clinician’s notes as a nonplanned procedure)
**Hypotheses 2 and 4**
1. Proportions of the following individual events at any point in the hospital stay after admission to the fourth floor:Emergent ICU transfer (emergent defined as urgent, unplanned)Emergent intubation (emergent is defined by clinician’s notes as a nonplanned procedure)3 units or more of blood ordered in 24 hoursinotropes or vasopressor useShock requiring inotropes or vasopressorsSepsis (sepsis-2 definition)Septic shock requiring inotropes or pressors (defined by a combination of the 2 above criteria)Cardiac arrestDeathDiuretic drip indicating congestive heart failure escalationInotropes or pressors for heart failureEmergent surgery prior to ICU transfer (emergent is defined by clinician’s notes as a nonplanned procedure)2. Hospital length of stay3. In patients who are never transferred to the ICU, the length of stay on the acute care floor4. ICU length of stay5. Proportion with readmission to hospital within 72 hours postdischarge6. In patients who meet the sepsis-2 criteria, the proportion of shock (ie, hypotension requiring inotropes or pressors), and death7. Number of days on intravenous antibiotics8. Number of days on intravenous anti-infectives9. Total duration of mechanical intubation (emergent and nonemergent)10. Impact of sex on outcome

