### Implementation and Education Considerations for Clinicians

All clinicians will be educated about CoMET to follow assessment guidelines in response to CoMET score. With consideration to alert fatigue, an increase of 2 or more within a period of 3 hours was selected as a guideline for assessment. In our retrospective cohort, a rise >2 units occurs 2 to 3 times per ward per day. On average then, a single nurse may experience 1 CoMET rise alert every 3 shifts. The clinicians will be provided education about what a score rising on either (or both) axes represents and the differential diagnoses to consider. This approach leaves the clinical context to that of the clinician and does not specify the specific diagnostics to order. The purpose of CoMET is to alert clinicians to prodromes or subtle physiological changes that precede overt clinical signs and draw attention to patients who may be in need of further attention, further clinical diagnostics, or escalation in care delivery. Clinicians may choose to draw a blood culture, initiate a rapid response team call, initiate oxygen therapy, or to do nothing but closely monitor or reassess the patient in an hour. Because CoMET models are trained on multiple events of clinical deterioration, clinicians understand the context of the CoMET score within the larger patient trajectory. There will be continual engagement and re-education throughout the entire study period across all clinician groups.

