**Hypotheses 3 and 4**
1. Time to the first order for transfusion of 3 units or more of blood ordered within 24 hours2. Time to first order for blood or urine culture obtained for suspicion of infection3. Time to first order for lactate drawn4. Time to first order for anti-infectives given for suspicion of infection5. Time to first order for fluid resuscitation given for suspicion of shock6. Time to rapid response team medical emergency team call initiation7. Time to first order for intravenous inotropes or vasopressors administered

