#### Outcome Ascertainment and Event Adjudication

Numerical and categorical data (lab values, timestamps, room transfers, etc) will be extracted in bulk from the University of Virginia clinical data warehouse and uploaded into a Research Electronic Data Capture (REDCap) database for outcome analyses. For nonautomated outcome elements, such as suspicion of infection, emergent status of intubations, surgeries or transfers, suspicion of shock, actual shock, indications for vasopressors, and others, protocol-trained clinical research coordinators (consisting of registered nurses or medical doctors) will individually review the electronic medical records of case and control participants.

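### Item 6 compares shock and death only among patients labelled septic, a group that the unmasked display may itself change, so a lower proportion need not mean that any patient benefited

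*Protocol article*

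**What the plan says.** All references are to the protocol article.

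- **Textbox 1, Hypotheses 2 and 4, item 6** sets this endpoint: "In patients who meet the sepsis-2 criteria, the proportion of shock" (low blood pressure needing inotropes or pressors) and of death. Item 1 of the same list counts, without restriction to septic patients, sepsis by the sepsis-2 definition, shock needing inotropes or vasopressors, septic shock (the combination of those two) and death.
- **Randomization Process** states that allocation is not masked once each assignment is implemented.
- **Implementation and Education Considerations for Clinicians** says the display should draw attention to changes that come before overt signs. Among the responses: "Clinicians may choose to draw a blood culture, initiate a rapid response team call, initiate oxygen therapy".
- **Textbox 1, Hypotheses 3 and 4** includes "Time to first order for blood or urine culture obtained for suspicion of infection", and time to anti-infectives given for the same reason. The Tertiary Hypothesis is that the display shortens such times.
- **Outcome Ascertainment and Event Adjudication** describes chart review: "For nonautomated outcome elements, such as suspicion of infection", coordinators "will individually review the electronic medical records of case and control participants".
- **Secondary Hypothesis** assigns yes-or-no outcomes to a GEE with logit link.

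**The concern.** Randomization makes the two arms comparable as groups of admissions. It does not make the septic patients in one arm comparable with the septic patients in the other if the intervention can change who is called septic. Here it plausibly can. The display is meant to prompt attention before overt signs, a culture is an expected reaction, and suspicion of infection is an outcome element taken from what clinicians wrote. The GEE handles correlation within clusters but does not correct for a denominator that differs between arms.

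At stake is the reading of item 6. A lower proportion with shock or death among septic patients could be reported as a benefit when the only change is that milder patients joined the denominator. The same extra detection would raise the item 1 sepsis proportion, which could be taken for harm.

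**Working it through.** The article gives no sepsis, shock or death rate for these endpoints, so there is no plan figure to reproduce. The numbers below show how the mechanism behaves under assumed inputs.

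**Inputs**
- From the article: 10,424 admissions (Sample Size, Power Analysis, and Attrition). With equal allocation (assumed), 10,424 / 2 = 5,212 per arm.
- Assumed: sepsis label in usual care s = 5%. The Introduction's 5% or more covers sepsis, hemorrhage and respiratory decompensation together, so it is only a loose anchor.
- Assumed: mortality m0 = 15% in patients labelled under usual care, and mx = 2% in the extra patients labelled only because of the display.
- Assumed: relative increase in labels e = 10% to 30%, with no true effect on any patient.

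**Formulas**
- Sepsis proportion with the display: s(1 + e).
- Death among septic patients with the display: (m0 + e·mx) / (1 + e).

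The second expression does not depend on s. Total deaths per arm are equal by construction.

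**Death among septic patients**

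| Extra labels | Calculation | Result | Ratio to 15% |
|---|---|---|---|
| 10% | (0.15 + 0.002) / 1.10 | 13.8% | 0.921 |
| 20% | (0.15 + 0.004) / 1.20 | 12.8% | 0.856 |
| 30% | (0.15 + 0.006) / 1.30 | 12.0% | 0.800 |

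The spurious relative reduction is therefore about 8% to 20%.

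**Would it show as significant?** Take e = 20% and ignore clustering.
- Septic patients: about 261 in usual care and 313 with the display. Pooled mortality is (39.1 + 40.1) / 574 = 13.8%. The standard error is √[0.138 × 0.862 × (1/261 + 1/313)] = 0.029, so z = 0.0217 / 0.029 ≈ 0.75.
- Sepsis proportion, 5.0% against 6.0%: the standard error is √[0.055 × 0.945 × 2/5,212] = 0.00447, so z = 0.010 / 0.00447 ≈ 2.24.

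On these inputs the apparent rise in sepsis is the easier of the two to detect. Clustering would lower both z values but would not remove the bias.

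**The same algebra for shock.** Assume s = 5%, e = 25%, shock risk 30% in usual-care sepsis and 5% in the extra cases. Shock among septic patients goes from 30% to (0.30 + 0.0125) / 1.25 = 25%, a ratio of 0.83. The chance of nominal two-sided significance is 25% to 27% with 4,639 to 5,212 admissions per arm (4,639 = 5,212 × 0.89, applying the 11% loss that the article states for the primary outcome). Varying e from 10% to 50%, and the extra cases' shock risk from 0% to 15%, moves the ratio between 0.95 and 0.67.

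**With all admissions as denominator**
- Shock and death per admission: no spurious difference.
- Septic shock per admission: 0.05 × 0.30 = 1.50%, against 1.50% + 0.05 × 0.25 × 0.05 = 1.56%. A small label effect remains.
- Sepsis plus death per admission (first example, e = 20%): 0.05 × 0.15 = 0.75%, against 0.75% + 0.05 × 0.20 × 0.02 = 0.77%.

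**The case against.** The strongest reply is that the effect is assumed. Nowhere does the article say that the display will label more, or milder, patients as septic. The Tertiary Hypothesis is about shorter time to response, not more work-ups. Item 1 counts events at any point in the stay, so recognizing the same patients sooner leaves the label unchanged. A culture is one option among several, and no action is mandated. If the extra cases were as severe as the usual ones, the ratio in item 6 would stay at 1. The article does not spell out sepsis-2 either, so its dependence on suspected infection is inferred from the chart-review section and the culture and anti-infective outcomes. The operational definition may be in the full protocol. All this stands, and it limits the point to what may happen.

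It also stands that the unconditional results are already listed in item 1, so a careful reader would have them next to item 6.

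The reply does not rescue item 6 as an inferential comparison. Its denominator is formed after randomization under open allocation, and the data could not separate a real benefit from extra detection.

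A reader might go further and infer that the distortion carries into the Hypothesis 4 costs. The Quaternary Hypothesis section does not support that. Its effect measures are in-hospital mortality and quality-adjusted life years, its costs come from warehouse cost data, and neither is tied to a sepsis label.

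**Conclusion.** The point holds as a limit on interpreting secondary endpoints. Item 6 cannot be read as an effect on septic patients, because the display may alter who belongs to that group. If it adds labels and the added cases are milder, the spurious relative reduction in death among septic patients is about 8% to 20% for 10% to 30% extra labels, given assumed mortality of 15% and 2%. It would often be non-significant. Whether labels will increase, and whether the extra cases will be milder, is not established by the article.

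A reader might infer that the display is bound to produce a false harm and a false benefit. The document supports only the possibility. The primary outcome has no sepsis component and is untouched.

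**What to change.** 1. Base between-arm inference for item 6 on all randomized admissions. Use the shock, septic shock and death proportions already in item 1, and add sepsis plus death per admission.
2. Keep the sepsis-conditional proportions of shock and death, labelled descriptive.
3. Report the item 1 sepsis proportion beside the culture-order rate per admission, and state that a higher count may reflect detection.

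Replacing the sepsis endpoint with culture-positive infection is not advised. It would still depend on cultures that the display may prompt, and it would lose culture-negative cases.

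The cost is wording and a minor analysis, because first culture orders are already an outcome under Hypotheses 3 and 4. Randomization began in January 2021, so the change should be dated and documented. The downside is that per-admission endpoints carrying the sepsis label have fewer events and keep the small residual effect shown above. All-admission shock and death are the protected comparisons.
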